**Attitudes towards HIV Risk Behaviors and Intimate Partner Violence**

We will ask participants their opinion on questions related to behaviors towards sex and sexual partners. These will be asked directly after similar questions assessing injunctive norms in their social network. Questions will ask opinions on condom use, concurrent partners, and whether there are occasions where hitting or being hit by a partner is ok. Responses are on a 4-point Likert scale from 1 = Strongly Agree to 4 = Strongly Disagree.

**Self-Control**

Self-control is a strong predictor of sexual risk behavior and IPV perpetration, and has been found to mediate the effects of community and family characteristics on violence perpetration. To assess self-control, we will use impulsivity and temper items from Grasmick et al.’s Self-Control Scale (1993). The scale was validated among males and females by Piquero and Rosay (1998) and was found to have good internal consistency (Cronbach’s a=.71).

**Sexual Network**

We will assess the sexual behaviors of participants with up to three partners with whom they have had the longest sexual relationship in the last year. Participants will first be asked to give the nickname of these partners, then will be asked about relationship longevity, confidence in condom negotiation, condom use, alcohol use before sex, concurrency, confidence in discussing HIV, HIV testing, and physical abuse.

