## 1.7 Rationale for Working with Camps

**Through an NIMH intervention development grant (R21 MH080577) our group identified viable locations and feasible strategies for intervening with high risk networks of men.** Using the PLACE methodology we identified and characterized 73 venues, locally named “camps,” where young men socialize within one ward of Dar es Salaam. While some health risk behaviors occur among camp members, camps are primarily constituted by entrepreneurial youth who use them as meeting spaces to provide one another with social support. Camps we surveyed had existed for an average of 8 years (range 4-13 years), had an average of 52 members between the ages of 15-40 years, and were formed by men who wanted to claim a space where they could engage in social activities such as soccer or playing pool. The 670 men in camps whom we interviewed reported substantial risk behaviors: 47% reported 2 or more sex partners in the past year; 47% of those who had ever had sex reported one or more concurrent sexual partnerships in the past six months; 21% had at least one symptom of an STI in the past 4 weeks; and 41% reported ever perpetrating physical or sexual violence against a female partner. The majority of men (73%) socialized in their camp daily for several hours, and over half (53%) were unemployed. Our qualitative research described how youth developed a democratic system for running the camps that minimally included a chairperson, a secretary and a treasurer.([Yamanis et al., 2010](#_ENREF_100)) Members paid dues to belong, and all camps maintained written membership records. In the second year of the grant, which was recently completed in August, 2011, we partnered with a microfinance organization to pilot a microfinance and health leadership intervention with men in three camps. Nineteen men received a two-week business training course, received loans of $100 each, participated in groups to guarantee loan repayment, and had weekly repayment sessions over 6 months. We also recruited 30 peer-nominated leaders from the three camps to participate in health leadership training that emphasized communication skills and strategies to influence peer behavior. Results of the pilot demonstrate the feasibility and acceptability of this multi-level approach. Only one of the 19 men who received a loan defaulted on his loan. We learned important strategies to motivate and support men through the repayment process, such as having more frequent repayment sessions, building ongoing business skill training into the regular repayment sessions, and providing more explicit instructions on record keeping. The twenty leaders who completed the initial two week training course on communication and social influence remained engaged in the pilot intervention for 9 months. Two additional booster training sessions, and maintenance of regular records of their communications with their peers about HIV and violence prevention were also part of the intervention.

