**Sexual concurrency**

We will assess concurrency during the two most recent sexual partnerships using the direct method. Participants are asked if they had sex with anyone else while in a sexual partnership with either of their two most recent partners. In our previous work in Tanzania, we found that the direct method was concordant with the UNAIDS calendar method at least 82% of the time([Eaton, 2009](#_ENREF_23)). We will ask participants how many sexual relationships they had at the same time during the past 6 months.

Concurrency in the last 12 months will also be assessed using an indirect method. Participants will be asked to list nicknames for their three longest sexual relationships in the past 12 months. For each partner mentioned participants will answer how recently they last had sex with each partner, when they first had sex with each partner, and if they are still having sex with each partner.

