***Interviewer:***

→ Now I would like to ask some more personal questions about you and your relationships. Please remember that your answers will be confidential.

| **No.** | **Questions and Filters** | **Coding Categories** | **Codes** | **Skip to:** | **VARIABLE** |
| --- | --- | --- | --- | --- | --- |
| Q1401 | Have you ever had sex?  • Vaginal sex is when a man puts his penis in the vagina of a woman; [some people call this [Swahili term].  • Anal sex is when a man puts his penis in the rectum of a man or a woman; [some people call this [Swahili term]. | NO  YES | 0  1 | **Q1409 and then AND SKIP to SECTION 16** | SEX_EVR |
| Q1402 | How old were you when you had sex for the first time? If you can’t recall the exact age, please give a best estimate. | __ __ YEARS  DON’T KNOW | 88 |  | SEX_AGE |
| Q1403 | How would you describe the first time that you had sex? Would you say that you wanted to have sex, you did not want to have sex but it happened anyway, or were you forced to have sex? | WANTED TO HAVE SEX  DID NOT WANT TO HAVE SEX BUT HAPPENED ANYWAY  WAS FORCED TO HAVE SEX | 1  2  3 |  | SEX_1DES |
| Q1404 | Did you experience any of the following types of situations the first time you had sex?  VERBAL THREATS  PHYSICAL THREATS  PHYSICAL FORCE/HOLDING DOWN  BEATING  HUMILIATING OR DEGRADING SEX ACTS | NO  YES | 0  1 |  | SEX1_VER  SEX1_PHY  SEX1_FRC  SEX1_DEG |
| Q1405 | In total, how many people have you ever had sex with in your lifetime? | __ __ # PERSONS |  | *Note that if this value is less than 3, the participant will only be asked about the corresponding # of partners in the Sexual Network Section | SEXE_NUM |
| Q1406 | In total, how many people have you had sex with in the past 12 months?  This includes people you had sex with only once and people you have had sex with regularly, such as a spouse or someone you live with.  If you can’t recall the exact number, please give a best guess. | NONE  __ __ # PERSONS | 0 |  | SXP12_NUM |
| Q1407 | How many of these partners were women and how many were men? | WOMEN___________  MEN___________ |  | **ASK ONLY IF Q100 = 1**  ***This should total Q1406** | MSM_NUM |
| Q1408 | In general, how would you consider your chances of getting HIV/AIDS? Are they small, moderate, great, or no risk at all? | NO RISK AT ALL  SMALL  MODERATE  GREAT | 1  2  3  4 |  | HIVRISK |
| Q1409 | Have you ever had a test for HIV/AIDS? | NO  YES  DON’T KNOW | 0  1  88 | **Q1501 (UNLESS Q1401 =0)** | TESTHIV |

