**NOTE: This section should only be asked for participants who have had sex (if Q1401=No, Skip this Section)**

*Interviewer:*

**→** I would now like to ask you about your sexual relationships. When I talk about having sex I mean that you had either vaginal or anal sex with the person.

Many people have different types of sexual partnerships. Some sexual partners are people we have sex with once or twice and some sexual partners are people we have sex with regularly. Some people have many sexual partners and other people have fewer sexual partners. Some people have sex with a partner of the same gender.

In the past 12 months, you mentioned that you have had sex with (Response from Q1406) people. I would like to begin by asking you about the person you have had the longest sexual relationship with during the last 12 months.

| **No.** | **Questions and Filters** | | **Coding Categories** | | **Codes** | **Skip to:** | **VARIABLE** |
| --- | --- | --- | --- | --- | --- | --- | --- |
| PARTNER #1 | | | | | | | |
| Q1501 | | Tell me about the person you have had the longest sexual relationship with. What is the nickname or initials I could use to talk about this person? | PARTNER #1 |  | | ASK ENTIRE SECTION ONLY IF Q1401=1 | NAME_P1 |
| Q1502 | | When was the most recent time you had sex with PARTNER 1? | YEARS AGO__ __  MONTHS AGO__ __  WEEKS AGO__ __  DAYS AGO__ __ |  | |  | RECSEX_P1 |
| Q1503 | | Is PARTNER 1 a man or a woman? | MAN  WOMAN | 1  2 | |  | GEND_P1 |
| Q1504 | | Where did you meet PARTNER 1? | HOME  SCHOOL  WORK  MY CAMP  ANOTHER CAMP  MOSQUE/CHURCH  STREET  CLUB/BAR  GUEST HOUSE  BEACH  PARTY  WEDDING/FUNERAL  OTHER___________________ | 1  2  3  4  5  6  7  8  9  10  11  12  13 | |  | MEET_P1  METP1_S |
| Q1505 | | How long have you been having sex with this partner? | YEARS_________________  MONTHS_______________  WEEKS_________________  DAYS__________________ |  | |  | SEXDY_P1  SEXDM_P1  SEXDW_P1 |
| Q1506 | | What type of relationship do you have with PARTNER 1? | SPOUSE  POLYGAMOUS SPOUSE  COHABITING PARTNER  GIRLFRIEND/BOYFRIEND  FRIEND  CASUAL ACQUAINTANCE  COMMERCIAL SEX WORKER  ONE TIME PARTNER  OTHER___________________ | 1  2  3  4  5  6  7  8  9 | |  | RELP_P1  RELP_P1_S |
| Q1507 | | To the best of your knowledge, how old is _____ PARTNER 1? | __ __ YEARS |  | |  | AGE_P1 |
| Q1508 | | Is PARTNER 1 a member of this camp? | NO  YES  DON’T KNOW | 0  1  88 | |  | CAMPM_P1 |

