| Q1540 | | Of these (Response from Q1539) times, how many times would you say you used a condom? | _____________ | |  |  | NUMCND_P2 |
| Q1541 | | Did you ever give PARTNER 2 money in exchange for having sex with you? | NO  YES | | 0  1 |  | GIVFSP_P2 |
| Q1542 | | Did PARTNER 2 ever give YOU money in exchange for having sex? | NO  YES | | 0  1 |  | RECFSP_P2 |
| Q1543 | | Did you use a condom the last time money was given or exchanged for sex with PARTNER 2? | NO  YES | | 0  1 | **ASK ONLY IF either Q1542 or Q1543 =1** | CNDM_P2 |
| Q1544 | | The last time you had sex with PARTNER 2, did you drink alcohol before or during sex | NO  YES | | 0  1 |  | DRNK1_P2 |
| Q1545 | | The last time you had sex with PARTNER 2, did PARTNER 2 drink alcohol before or during sex with you? | NO  YES  DON’T KNOW | | 0  1  88 |  | DRINK2_P2 |
| Q1546 | | While you were in a sexual relationship with PARTNER 2, did you have sex with anybody else? | NO  YES | | 0  1 |  | SXCUR_P2 |
| Q1547 | | As far as you know, during the time you were having a sexual relationship with PARTNER 2, do you think PARTNER 2 had sex with other people? | NO  YES | | 0  1 |  | MCP_P2 |
| Q1548 | | How confident are you that you can use a condom with PARTNER 2? | VERY CONFIDENT  SOMEWHAT CONFIDENT  NOT AT ALL CONFIDENT | | 1  2  3 |  | UCND_P2 |
| Q1549 | | How confident are you that you can discuss HIV with PARTNER 2? | VERY CONFIDENT  SOMEWHAT CONFIDENT  NOT AT ALL CONFIDENT | | 1  2  3 |  | TLKHIV_P2 |
| Q1550 | | Have you ever discussed getting an HIV test with PARTNER 2? | NO  YES | | 0  1 |  | TLKTST_P2 |
| Q1551 | | Have you ever gone together with PARTNER 2 for an HIV test? | NO  YES | | 0  1 |  | TOGTST_P2 |
| Q1552 | | Has PARTNER 2 shared the results of their HIV test in the past 12 months? | NO  YES | | 0  1 |  | TSTDISC_P2 |
| Q1553 | | In the past 12 months, has PARTNER 2 ever hit, slapped, kicked, pushed, shoved or otherwise physically hurt you? | NO  YES | | 0  1 |  | VICVIO_P2 |
| Q1554 | | In the past 12 months, have you ever hit, slapped, kicked, pushed, shoved or otherwise physically hurt PARTNER 2? | NO  YES | | 0  1 |  | PERVIO_P2 |
| PARTNER #3 | | | | | | | |
| Q1555 | | Tell me about another person you had sex with most recently before PARTNER 2. What is the nickname or initials I could use to talk about this person? | PARTNER #3 | |  |  | NAME_P3 |

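### Appendix D caps the partner blocks by lifetime rather than past-year partners, so partners from outside the last year can enter the sexual-network and 12-month concurrency measures

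*Protocol*

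**What the plan says.** Section 7.4.1 of the protocol defines two measures on a one-year window. Under Sexual Network, behaviour is assessed with "up to three partners with whom they have had the longest sexual relationship in the last year". Under Sexual concurrency, the indirect method has the same frame: "Participants will be asked to list nicknames for their three longest sexual relationships in the past 12 months".

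Appendix D collects these data as follows.

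- Q1405 asks "In total, how many people have you ever had sex with in your lifetime". The routing note for the partner blocks is attached to this item: "if this value is less than 3, the participant will only be asked about the corresponding # of partners in the Sexual Network Section".
- Q1406 asks "In total, how many people have you had sex with in the past 12 months". It allows the answer none, and no skip is attached. The count is only read back in the Section 15 lead-in.
- The only gate to Section 15 is "ASK ENTIRE SECTION ONLY IF Q1401=1", that is, ever having had sex.
- Partner 1: the lead-in refers to the last 12 months, but Q1501 itself has no limit and Q1502 accepts an answer in years.
- Partner 2: Q1528 is limited to the last 12 months.
- Partner 3: Q1555 reads "Tell me about another person you had sex with most recently before PARTNER 2", with no limit.

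Section 8.2.3 uses the same form at baseline, 12 months and 30 months.

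**The concern.** The definition depends on the past year and the routing depends on the lifetime. The two agree only for men whose past-year count equals their lifetime count, or is at least three.

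For other men the form opens more blocks than there are last-year partners. What goes into the surplus blocks matters because the items in them are not all tied to the calendar. Q1512 and Q1513 ask about the last month in which the man had sex with that partner, whenever that was, although section 7.4.1 describes condom use over the past month. Q1519 and its counterparts ask about concurrency during that relationship. For a partner last seen more than 12 months ago, both sets of answers describe behaviour from before the recall year. At the 30-month wave that means before about month 18 (30 − 12). At the 12-month wave it means around or before the start of the intervention.

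Such records would tend to dilute change in the per-partner condom and concurrency measures, which are secondary, and in sexual networks, which the protocol names as a mediator.

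**Working it through.** **Inputs.** L is lifetime partners (Q1405) and P is past-12-month partners (Q1406), both from Appendix D, Section 14. The previous-survey share comes from section 1.7: "47% reported 2 or more sex partners in the past year", among 670 men. Average camp composition comes from section 9.1.1: 36.2 sexually active males out of 52.

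**Blocks opened and blocks the definition allows.** For men who have had sex, the form opens up to min(L, 3). The definition in 7.4.1 implies min(P, 3). The surplus is min(L, 3) − min(P, 3).

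| Lifetime L | Past year P | Opened | Implied | Surplus |
|---|---|---|---|---|
| 1 | 0 | 1 | 0 | 1 |
| 1 | 1 | 1 | 1 | 0 |
| 2 | 0 | 2 | 0 | 2 |
| 2 | 1 | 2 | 1 | 1 |
| 2 | 2 | 2 | 2 | 0 |
| 3 or more | 0 | 3 | 0 | 3 |
| 3 or more | 1 | 3 | 1 | 2 |
| 3 or more | 2 | 3 | 2 | 1 |
| 3 or more | 3 or more | 3 | 3 | 0 |

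**What the surplus blocks hold.**

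- *P = 2, L at least 3.* Partners 1 and 2 can be the two last-year partners. Q1555 then asks, without a limit, for someone before Partner 2, so an older partner is a correct answer.
- *P = 1, L at least 2.* If Partner 1 is the last-year partner, Q1528 has no valid answer and the form prints no skip. If L is at least 3, Q1555 then refers back to a Partner 2 who does not exist. If Q1501 is answered as worded, with the longest relationship ever, an older partner can take block 1.
- *P = 0.* The lead-in asks for a last-year partner after reading back a count of zero. Q1501 on its own can be answered with an older partner, and Q1502 can record that in years.

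**Size.** In the previous survey, 100 − 47 = 53% of men had 0 or 1 past-year partners (0.53 × 670 ≈ 355). Men who never had sex skip Section 15 and must be taken off. Their share is not stated. If sexually active in section 9.1.1 means ever had sex, and that ratio applied to the surveyed men, then 36.2/52 = 69.6% have had sex, 30.4% have not, and 53 − 30.4 = 22.6% have 0 or 1 past-year partners and reach Section 15. If the term means recently active, the deduction is unknown.

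How many of these men have a surplus block depends on lifetime counts, which the protocol does not give. The answer runs from none (every man with one past-year partner has only ever had one, and every man with none has never had sex) to all of them. Men with exactly two past-year and three or more lifetime partners come on top. They are part of the 47%, and their share is not given either.

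**The case against.** The strongest reply is that little is lost for good. Q1406 counts past-year partners directly at each wave, and Q1502, Q1529 and Q1556 date the last sex with each partner, so the last-year network can be recovered by a filter. This stands. Such a filter may be laid down in an analysis plan that is not at hand. What remains is that the definition and the instrument in this one document do not match.

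A reader might infer that the measured last-year network cannot shrink after the intervention. The documents do not support that. A true lifetime count cannot fall, so the number of blocks opened cannot fall, but no section analyses the number of blocks, and Q1406 is free to fall.

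A reader might also infer that men are made to report old partners throughout. That does not fit Partner 2, which is limited to 12 months. The Q1405 note is a ceiling, and for a man with one past-year partner an empty block is a likely result. Older partners enter through the wording of Q1501 and Q1555 together with the missing past-year routing.

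Two further points stand. Section 7.4.1 defines consistent condom use on the three most recent partners and direct concurrency on the two most recent partnerships, with no one-year limit on which partners count. For these, a lifetime cap is defensible. And neither primary endpoint uses Section 15: STIs are measured by PCR and violence by the separate Section 8 items. Mediation is examined only if programme effects are found.

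**Conclusion.** The mismatch is real and can be read directly from the text. The sexual network and indirect concurrency are defined on the last year, while Appendix D caps the blocks by lifetime partners, has no skip for a past-year count of zero, and leaves Q1501 and Q1555 without a 12-month limit. If the records are not filtered, partners from outside the window can enter these two measures. The condom and concurrency answers for those partners would tend to dilute change in secondary measures and in the sexual-network mediator. The primary endpoints and the past-year partner count are not affected.

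No share of men or of blocks can be defended from the protocol. The ceiling is the 53% with 0 or 1 past-year partners, less men who never had sex, plus some with exactly two. It assumes that the previous survey's distribution carries over to this trial. The direction of the bias is reasoned from the item wording and its size is not estimated.

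**What to change.** For the last-year network and the 12-month concurrency measure:

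- Set the number of blocks to the smaller of 3 and Q1406, with none when Q1406 is zero.
- Put the same 12-month limit on Q1501 and Q1555 that Q1528 already has.
- For waves already collected, drop from these measures every partner whose last sex (Q1502, Q1529, Q1556) was more than 12 months ago.
- Keep older most-recent partners only where the consistent-condom-use definition or the direct concurrency measure in 7.4.1 needs them, and flag them by recency.

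The cost is one change to the tablet skip logic, two item wordings, one data filter and one recency flag. There will be slightly fewer partner records per man.

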**Perceived Social Support**

We will use the Adolescent Perceived Microsystems Scale for Social Support to assess emotional and material support ([Seidman et al., 1995](#_ENREF_81)) This scale, including a measure of support for sexual health information, demonstrated high reliability among youth in rural Kenya (α = .95).([Puffer et al., 2010](#_ENREF_69)) This study ranked received support on a 4-point Likert scale. For our study participants will answer Yes or No regarding support they receive from family members, relatives, peers and sexual partners.

**Social Network Norms (For partner violence, condom use, HIV testing and concurrency)**

We hypothesize that the positive influence of peers will promote reductions in risk behavior by participating camp members. To obtain information regarding peer influence, we first will ask participants to identify all members of the camp that they know, then to select their three closest friends out of those selected. For each of the three people mentioned, we will ask the participant to describe whether the person uses condoms consistently, has ever perpetrated violence towards their partners, has had an HIV test, has ever engaged in at least two sexual partnerships at the same time, and whether or not the friend condones these behaviors in others.

**Camp Norms**

We will also ask participants questions about norms in the camp as a whole, using four questions informed by the Add Health Survey, which was used to assess adolescents’ perceptions of their peers’ substance use (Henry et al., 2011).

**Moral Agency**

At midpoint and endpoint we will assess moral agency in protecting against HIV transmission. Questions will be adapted from the Personal Responsibility Scale. ([Wolitski, Flores, O’Leary, Bimbi, & Gomez, 2007](#_ENREF_99)) Factor analysis of the scale revealed two factors, personal responsibility and partner responsibility. Computed item-to-total correlations for each scale were high and statistically significant. Personal responsibility questions were internally consistent (a = .85), while internal consistency for partner responsibility was relatively poor (a = .58). These questions ask participants about individual responsibility in protecting others against HIV. Responses are on a 5-point Likert scale from 1 = Strongly Agree to 5 = Strongly Disagree.

## 7.5 Mediating Variables/Outcomes

Mediating variables will be measured at baseline, 12 months and 30 months.

**Hope**

We will use Snyder’s State Hope Scale ([C. R. Snyder et al., 1991](#_ENREF_88)), a 6-item measure that has been shown to be internally consistent among several populations.([C. R. Snyder et al., 1996](#_ENREF_89)) Hopelessness among young urban men is associated with greater violence later in adolescence ([Stoddard, Henly, Sieving, & Bolland, 2011](#_ENREF_91)). We translated the measure into Kiswahili and found that a 5-item version was reliable in our R21 (n = 75; α = .73). We will use the 5-item version.

